## Abstract

Cervical spondylotic radiculopathy (CSR) is the most common type of cervical spondylosis, accounting for about 60% of the incidence of cervical spondylosis. Both cervical traction and traditional Chinese medicine hot compress are common and effective treatment for CSR. This study will be performed to investigate the effect of a combination of cervical traction and traditional Chinese medicine hot compress on CSR. In this non-blinded, randomized controlled trial, 100 eligible patients will be randomly divided into a treatment group (intermittent cervical traction combines with traditional Chinese medicine hot compress) and a control group (intermittent cervical traction combined with hot compresses). Before and after the intervention, the Visual Analog Scale score, Neck Disability Index score, and 20-score scale of symptoms will be evaluated at baseline and at 7, 14, 21, and 28 days. During the treatment period, any signs of acute adverse events, such as paralysis of aggravated pain, nausea, dizzy, and even syncope, will be recorded at each visit. Although intermittent cervical traction and traditional Chinese medicine hot compress have been used in the treatment of CSR in China for many years, there is no consensus on its effectiveness of combination therapy. This experiment will provide convincing evidence of the efficacy of intermittent cervical traction combined with traditional Chinese medicine hot compress in the treatment of CSR.

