#### Randomization and allocation

2.1.5

After screening, patients will be randomly divided into 2 groups with a 1:1 allocation ratio. Randomization will be based on the Statistical Social Science Software Package (SPSS) software (version 21.0), generating random numbers, and patients will be randomly divided into treatment group (50 cases) and control group (50 cases).

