#### Outcome measurement

2.1.6

Pain is one of the most common reasons for patients with CSR to see a doctor. Therefore, the Visual Analog Pain Scale (VAS) will be chosen as the main outcome measure for the assessment of the neck and upper limbs. The VAS score is a reliable and effective method of pain measurement. There is a 100 mm long horizontal line. The left side records “no pain” (score 0), and the right side records “pain is severe and intolerable” (score 10). The patient is required to place a mark corresponding to its current pain level on the horizontal line (the most severe pain at rest and during exercise),^[11]^ and then determine the VAS score by measurement.

Neck Disability Index (NDI)^[12]^ is one of the most commonly used indexes to evaluate patients neck dysfunction. The NDI score includes 4 subjective symptoms (neck pain intensity, headache, concentration, sleep) and 6 items related to activities of daily living (weightlifting, work, driving or cycling, entertainment, personal care, reading). Each item has 6 levels of responses, each with a score of 0 to 5, 0 means no disability, 5 means severe disability. The lowest total NDI score is 0 points, and the highest is 50 points; the higher the score, the more serious the degree of dysfunction. This study adopted all dimensions of NDI score.

Tanaka Yasuhisa Cervical Spondylopathy Symptom Scale is the “Nerve Root Cervical Spondylopathy Symptom Scale” proposed by the Japanese scholar Hisasu Tanaka. It compares the improvement index before and after treatment for evaluation: improvement rate = (points after treatment-points before treatment)/(20 -Points before treatment)∗100%.

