#### Statistical analysis

2.2.1

Trained statisticians will use intentional processing methods for effectiveness and safety analysis. In addition, the final outcome observation index method will be applied to deal with missing values. All statistical analysis will be performed by the SPSS 21.0. The statistical test is two-way, *P* < .05 is statistically significant. The mean ± standard deviation will be used to describe continuous variables. This percentage is used to describe the variable. Continuous variables that follow a normal distribution will be analyzed by Student *t* test; otherwise, nonparametric tests will be used to compare group differences.

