#### Data collection and monitoring

2.2.2

This is a 4-week clinical trial. Participants need to conduct a 4-week research intervention during a 4-week follow-up. Five rounds of disease activity assessment (baseline and week 1, 2, 3, and 4) will be independently recorded by 2 investigators in Epidata (version 3.1), and differences will be resolved through discussion and a third research institute. Longhua Hospital affiliated to Shanghai University of Traditional Chinese Medicine is responsible for monitoring and quality control.

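### The main VAS comparison is planned without baseline adjustment, and its test is picked by the observed distribution: valid, but inefficient and not fixed in advance

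*Protocol article*

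**What the plan says.** The Statistical analysis section (2.2.1) holds the only analysis text in the article. For between-group comparisons it says "Continuous variables that follow a normal distribution will be analyzed by Student" t test. For variables that are not normal, it says "otherwise, nonparametric tests will be used to compare group differences". On the level it says "The statistical test is two-way, *P* < .05 is statistically significant", which I read as two-sided 0.05. It names no covariate, no normality test or threshold, and no specific nonparametric test.

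Other sections supply the design facts:

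- Outcome measurement: "the Visual Analog Pain Scale (VAS) will be chosen as the main outcome measure".
- Abstract: "the Visual Analog Scale score, Neck Disability Index score, and 20-score scale of symptoms will be evaluated at baseline and at 7, 14, 21, and", the last of these assessments being on day 28.
- Data collection and monitoring: "Five rounds of disease activity assessment (baseline and week 1, 2, 3, and 4").
- Randomization and allocation: "patients will be randomly divided into treatment group (50 cases) and control group (50 cases").
- Outcome measurement, for the symptom scale only: "improvement rate = (points after treatment-points before treatment)/(20 -Points before treatment"), times 100%.

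Nothing says whether VAS and NDI enter the test as final values or as changes from baseline.

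**The concern.** A two-sample t test or rank test has no place for a baseline covariate. Every patient has a baseline VAS and NDI, so part of the outcome variation that baseline could explain stays in the error term. With 100 patients in all, the lost precision may matter.

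The second issue is pre-specification. The choice between t test and rank test is made from the observed distribution, and four post-baseline visits are planned. The same outcome could get a t test at one visit and a rank test at another. The two address different quantities: a rank test does not directly estimate a mean difference in VAS points with an interval. The effect measure for the main outcome is therefore settled only once the data are seen.

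This objects to a method the article states. It does not object to detail left to a fuller document, because a later plan using ANCOVA would have to depart from the stated tests.

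**Working it through.** **Inputs from the article.** 50 per arm; two-sided 0.05; VAS as main outcome; baseline plus four later assessments.

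**Inputs assumed.** Correlation r between baseline and follow-up score of 0.3, 0.5 or 0.7. Standardised effect d = 0.5, in units of the SD of the final score. The SD is taken as equal at baseline and follow-up.

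**Plan's own figure.** The total of 100 cannot be reproduced, because no effect size, SD, power or dropout is printed with it. As a reference point (normal approximation), a final-value test with 50 per arm has 80% power at d = (1.96 + 0.84) × √(2/50) = 0.56.

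**Step 1: variance.** With the SD set to 1, the outcome variances are:

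- final value: 1
- change: 2(1 − r)
- ANCOVA: 1 − r²

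The ratio of ANCOVA to final value is 1 − r². The ratio of ANCOVA to change is (1 − r²)/[2(1 − r)] = (1 + r)/2.

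| r | ANCOVA / final value | Cut | ANCOVA / change | Cut |
|---|---|---|---|---|
| 0.3 | 1 − 0.09 = 0.91 | 9% | 1.3/2 = 0.65 | 35% |
| 0.5 | 1 − 0.25 = 0.75 | 25% | 1.5/2 = 0.75 | 25% |
| 0.7 | 1 − 0.49 = 0.51 | 49% | 1.7/2 = 0.85 | 15% |

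Against a final-value test, 100 patients analysed by ANCOVA are worth 100/0.91 = 110, 100/0.75 = 133 or 100/0.51 = 196 patients analysed without adjustment.

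**Step 2: power.** I used the two-sample t test with 50 per arm and an effective standardised effect of d for final values, d/√[2(1 − r)] for changes and d/√(1 − r²) for ANCOVA, at d = 0.5.

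| r | Effective d: final / change / ANCOVA | Power: final | Power: change | Power: ANCOVA |
|---|---|---|---|---|
| 0.3 | 0.50 / 0.42 / 0.52 | 70% | 55% | 74% |
| 0.5 | 0.50 / 0.50 / 0.58 | 70% | 70% | 82% |
| 0.7 | 0.50 / 0.65 / 0.70 | 70% | 89% | 93% |

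The one degree of freedom that ANCOVA spends on the covariate does not change these rounded figures.

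**Step 3: does the normality switch inflate type I error?** It was simulated with a Shapiro test in each arm, then a t test or Mann-Whitney test, 50 per arm, 10,000 runs per scenario. The rejection rate under no effect was 4.8% for normal data, 5.1% for VAS-like data clipped at 0 and 5.2% for gamma data. The rank test was selected in 9%, 82% and nearly 100% of runs respectively. The error rate holds, but which test is run depends heavily on the shape of the data.

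**The case against.** The strongest defence is that the planned comparison is sound. In a 1:1 randomised trial an unadjusted test is unbiased, and its standard error already allows for chance baseline differences. That stands. The SD of the baseline difference is √(2/50) = 0.2 SD, so a gap above 0.3 SD has a probability of about 13%, but this is not a further cost on top of the larger standard error.

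Four stronger readings are tempting, and the article does not support them.

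- **All baseline scores are thrown away.** For the symptom scale this is wrong: the improvement rate uses the pre-treatment score in both numerator and denominator. For VAS and NDI it is one reading only. If changes are tested, baseline is used, though less efficiently than in ANCOVA.
- **The gain is as large as the final-value comparison suggests.** At r = 0.7, power rises from 70% to 93% only if final values are tested. Against changes it rises from 89% to 93%. At r = 0.3 the order reverses, and the larger gain is against changes.
- **Choosing the test from the data inflates false positives.** The simulation shows no sign of this.
- **A rank test would leave no result in VAS points.** The article commits to mean and SD for continuous variables, so group means would still be available. What would be missing is an interval tied to the test.

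An analysis plan that is not shown may specify adjustment. That does not remove the point, because the published text names the unadjusted tests.

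**Conclusion.** The point holds for VAS and NDI as a matter of efficiency and pre-specification. It does not show invalidity. Over the assumed correlations of 0.3 to 0.7, ANCOVA has lower variance than either version of the unadjusted t test, by 9% to 49% against final values and 15% to 35% against changes. At d = 0.5 the gain in power is about 4, 12 or 24 points against final values (from 69.7% to 73.7%, 81.6% or 93.4%), and about 18, 12 or 4 points against changes (from 55.3%, 69.7% or 89.2%). The direction is secure over this range. The size is not, because r and d are assumptions and the article supplies neither.

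The unfixed test and effect measure for the main outcome do not depend on those assumptions. The symptom-scale improvement rate lies outside the point. Severity: should-fix; a free improvement.

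**What to change.** Replace the test-selection sentence for VAS and NDI with wording such as: *The primary analysis compares VAS between groups at [one pre-specified time, for example day 28, the end of treatment] by ANCOVA with treatment group and baseline VAS as terms, and reports the adjusted mean difference with its 95% confidence interval. NDI is analysed in the same way with baseline NDI. The method does not depend on a normality test. A named rank-based test is a sensitivity analysis only.*

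The primary time is a real decision for the investigators, since the article names VAS but no single time. Name one model and do not offer a repeated-measures mixed model as interchangeable: with missing data the two differ, and the article's rule for missing values, which reads as carrying the last observation forward, would not be used in a mixed model. Leave the symptom-scale improvement rate as defined unless the investigators choose to revisit it separately.

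The cost is one paragraph, settled before the comparative data are analysed. No new data are needed, and the planned SPSS 21 runs ANCOVA.

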#### Data collection and monitoring

2.2.2

This is a 4-week clinical trial. Participants need to conduct a 4-week research intervention during a 4-week follow-up. Five rounds of disease activity assessment (baseline and week 1, 2, 3, and 4) will be independently recorded by 2 investigators in Epidata (version 3.1), and differences will be resolved through discussion and a third research institute. Longhua Hospital affiliated to Shanghai University of Traditional Chinese Medicine is responsible for monitoring and quality control.

#### Quality control

2.2.3

Before conducting the study, we will conduct unified training to ensure that all relevant doctors, nurses and evaluators fully understand the entire trial process. In order to ensure the quality of the entire study, 2 supervisors will be sent every month to ensure that the enrolled patients meet the inclusion criteria and do not meet the exclusion criteria; the research group recruits enough patients to participate in the study; all enrolled patients fully follow the clinical trial Process, perfect the case report form (CRF), follow the standard operating procedure (SOP). During the entire treatment and follow-up period, the inspector will record the dropout, withdrawal, and related reasons in detail, and record any compliance of all patients.

## Discussion

3

The clinical features of CSR are that the pain range is consistent with the compressed spinal nerve area, mainly pain, numbness, and hypoesthesia. In severe cases, radicular weakness, and muscle atrophy may occur. After the occurrence of CSR, a large number of inflammatory factors are released from the damaged tissue, which stimulates the nerve root and causes radicular pain symptoms.^[13]^ At the same time, it activates a variety of cell signal transduction pathways, cytokines and receptor proteins in the body, which in turn can induce interleukin-1β (IL-1β), interleukin-6 (IL-6), and tumor necrosis factor- α (TNF-α) and other pro-inflammatory cytokines are secreted to mediate inflammation and form a vicious circle of inflammation.^[13]^ The heat generated by herb compresses causes blood vessels to dilate and muscles relax. Heat therapy is a common alternative therapy to improve blood circulation and local muscle spasms. The various ingredients of herb have a variety of analgesic and anti-inflammatory properties. The herb in this research contain Corydalis, Yang Bin, etc.^[14]^ When studying the extracts of Chinese medicine Corydalis Corydalis, they found that Corydalis extracts can exert the same effect as NLRP3 inhibitors. Inhibit NLRP3 inflammasome signaling pathway protein expression. The NLRP3 inflammasome signaling pathway can be widely involved in the body's inflammatory response and promote the synthesis and secretion of inflammatory factors such as prostaglandin E2 (PGE2), phospholipase A2 (PLA2), IL-6, and TNF-α.^[15]^ Corydalis extract inhibits NALP3 and then inhibits the inflammatory response, relieves the inflammatory response caused by nerve root compression, and reduces secondary spinal cord injury.

Traditional Chinese medicine can not only inhibit nerve root inflammation, relieve nerve root edema, and fundamentally alleviate the root symptoms of CSR, but also can increase the body's pain threshold, improve the body's spontaneous pain and hyperalgesia caused by inflammatory stimulation,^[16]^ and relieve it quickly. The first symptoms of CSR are contradictory. The active ingredient xanthamide extracted from Zanthoxylum bungeanum can significantly increase the pain threshold of the CSR body, so that the body can withstand greater intensity of pain stimulation. Moreover, prickly amide can reduce the levels of inflammatory factors TNF-α, IL-1β, and cyclooxygenase-2 (COX-2), play an anti-inflammatory and analgesic effect, and have a certain control effect on the symptoms of CSR [24]. The active ingredient ferulic acid (FA) extracted from Ligusticum chuanxiong can also increase the pain threshold of the CSR body, and Zhao Weihong and others have observed that FA can significantly improve the obvious edema and degeneration of nerve root tissue and demyelination caused by lesions. To improve the potential motor conduction velocity (MCV) of the median nerve of the CSR body.^[17]^

Therefore, we plan to conduct this prospective randomized controlled clinical trial to study the clinical efficacy of traditional Chinese medicine hot compress combined with traction in the treatment of cervical spondylotic radiculopathy, and to explore how to use the most combination of conservative therapies to improve cervical pain and cervical radiculopathy. Radical symptoms and explore whether it can be the first choice for potential conservative treatment of CSR.

## Abbreviations

Abbreviations: COX-2 = cyclooxygenase-2, CRF = case report form, CSR = cervical spondylotic radiculopathy, FA = ferulic acid, IL-1β = interleukin-1β, MCV = motor conduction velocity, NDI = Neck Disability Index, TNF-α = tumor necrosis factor- α, VAS = Visual Analog Scale.
